### Outcomes

#### Primary outcome

The primary outcome is the live birth rate, defined as delivery of any viable infant after 28 weeks of gestation.

#### Secondary outcomes

The secondary outcomes include ovulation rate, conception rate, pregnancy rate, pregnancy loss rate, changes in hormonal/metabolic parameters, changes in QOL scores, and changes in AEs.

#### Ovulation rate

The ovulation rate per participant and per cycle will be analyzed. Ovulation will be defined when the serum progesterone level on day 21 or day 28 of the cycle is > 3 ng/ml. The ovulation rate per participant will be calculated as the proportion of women who ovulated at least once during the treatments among the total women in the primary analysis. The ovulation rate per cycle will be calculated as the proportion of cycles in which ovulation occurs among all tested cycles in the primary analysis.

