#### Letrozole

Women in the letrozole group will receive letrozole without acupuncture. One pill of letrozole (2.5 mg) (Femara; Novartis Pharmaceuticals, Basel, Switzerland) will be started between days 3 and 7 of the spontaneous menstrual cycle or between days 3 and 7 after a withdrawal bleeding following progestin. After the initial dose, one pill will be taken for the next 4 consecutive days (five pills total). If there is a response with ovulation (i.e., the serum progesterone level on day 21 or day 28 of the cycle is > 3 ng/ml), this dose will be maintained and will be given between days 3 and 7 of the next cycle. In those with no ovulatory response, day 28 of the cycle will be regarded as day 1 of the next cycle. For the new cycle, letrozole will be started on day 1, and the letrozole dose will be increased to 5 mg (two pills) per day for 5 consecutive days. If there is still no response, the dose will be increased to 7.5 mg (three pills) per day for 5 days in the next cycle. The maximum daily dose of letrozole will be 7.5 mg daily for 5 consecutive days.

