### Treatment visits

The women will be instructed to engage in intercourse once every 2 or 3 days. A serum progesterone measurement will be taken in the local laboratory on day 21 of the menstruation cycle. An elevated progesterone level > 3 ng/ml will be considered to indicate evidence of ovulation. If there is no ovulation, the serum progesterone level will be checked every week until ovulation. If ovulation occurs, a serum pregnancy test will be performed 1 week later. For the duration of the treatment, urine LH or human chorionic gonadotropin (HCG) levels can be measured, depending on the judgment of the PI, in order to obtain timely information on ovulation or pregnancy and thus to instruct the participant to continue engaging in intercourse or to stop the intervention. We will determine whether the women have an ovulation response based on the serum progesterone level, and there will be three possible scenarios—ovulation, delayed ovulation, or no ovulation—as follows:
*Ovulation*: Serum progesterone level on day 21 of the cycle > 3 ng/ml. A serum pregnancy test will be performed 1 week later to exclude pregnancy. In the letrozole and placebo letrozole groups, letrozole or placebo letrozole will be started between days 3 and 7 of the new cycle, and the letrozole or placebo letrozole dose will be maintained at the same level as the previous cycle.*Delayed ovulation*: Serum progesterone level on day 21 of the cycle < 3 ng/ml. In this case, we will wait 1 week and then check the serum progesterone level again. If the second measurement shows that ovulation occurred (serum progesterone > 3 ng/ml), a serum pregnancy test will be performed 1 week later to exclude pregnancy. In the letrozole and placebo letrozole groups, letrozole or placebo letrozole will be started between days 3 and 7 of the new cycle, and the letrozole or placebo letrozole dose will be maintained.*No ovulation*: Negative serum progesterone on day 21 and day 28. In the letrozole and placebo letrozole groups, women will take letrozole or placebo letrozole on day 28 of the cycle, and then one more tablet per day will be given for 5 consecutive days until the maximum daily dose of three tablets per day. Day 28 will be defined as day 1 of the next cycle, and a serum progesterone measurement will be made every week until ovulation.

Every menstruation will be recorded, including the date, amount, and duration of menstruation.

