### Data analysis

The primary analysis will use an intention-to-treat approach to examine differences in the live birth rate among the four treatment groups. Primary efficacy analysis will be performed by comparing the treatment groups with respect to the primary outcome of live birth using the Pearson chi-square test. For the secondary supportive analysis, we will fit a logistic regression model to compare the treatment arms with respect to the primary outcome of live birth, adjusting for other factors such as randomization stratification of study site and prior exposure to study medications. Comparisons of variables such as live birth rate, ovulation rate, conception rate, pregnancy rate, multiple pregnancy rate, and miscarriage rate will include relative risk and 95% confidence intervals in addition to the chi-square test. Changes in laboratory values will be assessed by analysis of covariance (ANCOVA).

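### Ovulation is counted only from day 21 or day 28 progesterone although weekly tests run until ovulation, and the cycle unit and per-cycle test are not fixed

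*Protocol article*

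**What the plan says.** All references are to the protocol article.

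- **Endpoint (Ovulation rate).** "Ovulation will be defined when the serum progesterone level on day 21 or day 28 of the cycle is > 3 ng/ml". Two rates follow. The per-participant rate is the "proportion of women who ovulated at least once during the treatments among the total women in the primary analysis". The per-cycle rate is "the proportion of cycles in which ovulation occurs among all tested cycles in the primary analysis".
- **Testing (Treatment visits).** The first progesterone test is on day 21. Then: "If there is no ovulation, the serum progesterone level will be checked every week until ovulation". No arm is excluded and no last day is given.
- **Restart at day 28.** The Letrozole section says: "In those with no ovulatory response, day 28 of the cycle will be regarded as day 1 of the next cycle". The Placebo letrozole section adopts the same schedule. Treatment visits, under its no-ovulation scenario, says: "Day 28 will be defined as day 1 of the next cycle, and a serum progesterone measurement will be made every week until ovulation". That sentence names no arm, but it follows one limited to the two pill groups.
- **Length of treatment.** Acupuncture runs for up to 16 weeks (Intervention). The End-of-treatment visit and Conception rate sections speak of four cycles for all women.
- **Test (Data analysis).** "Comparisons of variables such as live birth rate, ovulation rate, conception rate, pregnancy rate, multiple pregnancy rate, and miscarriage rate will include relative risk" with 95% confidence intervals and a chi-square test. The two ovulation rates are not separated. A later paragraph promises correlated-data methods for secondary outcomes repeated over time. Its example is a linear mixed model for hormone levels, and per-cycle ovulation is not named.

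**The concern.** Hypotheses 1 to 3 in Objectives each claim an effect on ovulation as well as on live birth, so the ovulation rates carry confirmatory weight even though they are secondary. Three features weaken them.

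1. The endpoint uses fewer tests than the schedule collects. Entry requires intervals over 35 days or fewer than eight bleeds a year, or, for amenorrhea, intervals over 90 days. A first positive after day 28 is to be expected in such women.
2. If the day-28 restart applies only to the pill arms, a long anovulatory stretch there becomes several tested cycles, while under acupuncture it stays one. The per-cycle denominator would then depend on the arm, and so would the number of chances to be counted as ever ovulating.
3. Cycles from one woman are correlated. A plain chi-square on cycles treats them as independent and gives P values that are too small and intervals that are too narrow.

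**Working it through.** **The plan's own figures.** The article gives no expected ovulation rate or power for ovulation. Its figures on cycles agree with each other: 16 × 7 = 112 days, and 112 / 4 = 28 days per cycle. The 45-pill maximum over four cycles is 5 × (1 + 2 + 3 + 3) = 45.

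**Step 1. Which first positives count.** Tests fall on days 21 and 28, then weekly. After a restart, the tests one and two weeks later are days 7 and 14 of the new cycle (8 and 15 if day 28 is literally day 1). The next two are taken as the new day-21 and day-28 tests.

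| First positive on day | No restart | Restart at day 28 |
|---|---|---|
| 21 or 28 | counted | counted |
| 35 or 42 | not counted | not counted |
| 49 or 56 | not counted | counted |

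The middle row holds on every reading. The last row depends on the scope of the restart.

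**Step 2. What a pill-only restart would do.** This is a simulation on assumptions, with no true difference between arms and only day 21/28 positives counted. Ovulation comes 10 days after cycle start plus an exponential wait. The woman-specific mean wait averages 10 to 80 days (between-woman CV 0.5 or 1.0). Progesterone is positive 3 to 12 days after ovulation, and the next natural cycle starts 14 days after ovulation. Follow-up is 112 days, with 20,000 women per setting.

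| Mean wait, CV | Tested cycles per woman (no restart / restart) | Per-cycle rate | Women counted as ovulating | Women who ovulated by day 112 |
|---|---|---|---|---|
| 10, 0.5 | 3.06 / 3.46 | 0.807 / 0.704 | 0.935 / 0.919 | 0.999 / 0.999 |
| 40, 0.5 | 2.11 / 3.55 | 0.393 / 0.314 | 0.516 / 0.716 | 0.910 / 0.911 |
| 40, 1.0 | 2.41 / 3.59 | 0.576 / 0.435 | 0.615 / 0.747 | 0.899 / 0.899 |
| 80, 0.5 | 1.70 / 3.68 | 0.229 / 0.192 | 0.295 / 0.542 | 0.741 / 0.746 |

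Over all eight settings the restart lowers the per-cycle rate by 4 to 14 points. It changes the share of women counted as ovulating by −2 to +25 points. The two rates can therefore move in opposite directions.

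The last two columns bound what the two-test rule misses. In the second row the shortfall is 0.910 − 0.516 = 0.394 without restart and 0.911 − 0.716 = 0.195 with it. These are upper bounds, because some of those ovulations come too late in the 112 days to be tested.

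**Step 3. A plain chi-square on cycles.** With m cycles per woman and within-woman correlation ICC, the design effect is DE = 1 + (m − 1) × ICC. The true two-sided error of a nominal 5% test is 2 × (1 − Φ(1.96 / √DE)). ICC is assumed.

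| ICC | DE, m = 2 | Type I error | DE, m = 4 | Type I error |
|---|---|---|---|---|
| 0.1 | 1.1 | 6.2% | 1.3 | 8.6% |
| 0.2 | 1.2 | 7.4% | 1.6 | 12.1% |
| 0.3 | 1.3 | 8.6% | 1.9 | 15.5% |
| 0.5 | 1.5 | 11.0% | 2.5 | 21.5% |

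Four cycles is the maximum, and treatment stops at pregnancy, so many women will contribute fewer.

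**The case against.** The strongest reply is that the restart is common to all arms. Treatment visits introduces its scenarios for the women in general and adds a pill-group prefix where a step concerns pills. The restart sentence has no such prefix and is joined to weekly testing, which every arm has. Four cycles for all women in 16 weeks also implies 28-day cycles throughout. This is a good reading, perhaps the better one. It means that arm-specific cycles are an ambiguity to resolve and not an established fault. It does not rescue positives one or two weeks into a restarted cycle.

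Second, days 21 and 28 are used consistently in the Letrozole, Treatment visits and Ovulation rate sections. That is true, and it suits a rule for deciding the next step of treatment. An outcome need not share that cut-off when further tests are scheduled.

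Third, a chi-square fits the per-participant rate, the correlated-data statement may be meant to cover the per-cycle rate, and the exact model can be left to an analysis plan. This also stands in part. What remains is that the article's stated test covers ovulation rate without saying which one, just after defining two.

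A reader might go further and infer that ovulation rates are not comparable across arms, that a false needle-versus-pill difference is likely, or that repeated cycles will certainly enter a chi-square. The text supports none of these. Letrozole and placebo share one schedule, and the two acupuncture arms share another, so hypothesis 2 is untouched by any restart difference. Nor can the worst cases be combined: one long acupuncture cycle per woman and four cycles per woman cannot both describe the same arm.

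**Conclusion.** The point holds in limited form.

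- **On every reading:** scheduled positives outside days 21 and 28 are observed and not counted.
- **If the restart is pill-only:** the cycle denominator differs between acupuncture and pill arms, which affects hypotheses 1 and 3. Under the assumptions of Step 2 this alone moves the per-cycle rate by 4 to 14 points. If the restart is common to all arms, this part falls away.
- **If a plain chi-square is used on cycles:** type I error is about 6 to 11% with two cycles per woman and 9 to 22% with four, for an assumed ICC of 0.1 to 0.5.

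The ICC, waiting times and progesterone window are assumptions, since the article gives no values. The outcome is secondary and the live birth analysis is unaffected. The change should be made, but it does not threaten the trial's main result.

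**What to change.** 1. For the endpoint, count ovulation as progesterone > 3 ng/ml at any scheduled weekly test.
2. Make the per-woman rate over the same 16-week window in all four arms the key ovulation outcome.
3. Reconcile the Letrozole, Treatment visits and Ovulation rate sections so that cycle has one endpoint definition in all arms, and state whether the day-28 restart covers the acupuncture arms. No dosing rule need change.
4. Analyse repeated ovulation with GEE or a mixed logistic model clustered on the woman. Keep the chi-square, relative risk and interval for the per-woman rate only.

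The cost is wording in the outcome and analysis sections, ideally settled before unblinding. The weekly progesterone results are already scheduled, so no new data are needed.

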#### Conception rate

Conception will be defined as a positive serum β-HCG measurement. Thus, the cumulative conception rate will be the proportion of women who conceive during the four treatment cycles among all women in the primary analysis.

#### Pregnancy rate

Pregnancy will be defined as an intrauterine pregnancy with fetal heart motion as determined by transvaginal ultrasound. The cumulative pregnancy rate will be the proportion of pregnant women among the total participants in the primary analysis.

#### Pregnancy loss rate

Pregnancy loss will be defined as pregnancy loss occurring from conception to 27 completed weeks of gestational age in this trial, including pregnancy loss in the first trimester, pregnancy loss in the second or third trimester, biochemical pregnancy loss, and ectopic pregnancy. The pregnancy loss rate will be the proportion of women who abort among all participants who conceive.

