## Objectives

The objectives of the present trial are to test the following four hypotheses:
Letrozole is more likely than personalized acupuncture to induce ovulation and to result in live birth.Personalized acupuncture is more likely than fixed acupuncture to induce ovulation and to result in live birth.Fixed acupuncture is more likely than placebo letrozole to induce ovulation and to result in live birth.Personalized acupuncture is more likely than letrozole, fixed acupuncture, and placebo letrozole to reduce the miscarriage rate and the risk of pregnancy complications.

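### The only defined pregnancy loss rate is conditional on conception, so it cannot carry hypothesis 4 as a randomized comparison, and its definition does not fit the other 28-week wording

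*Protocol article*

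**What the plan says.** In the protocol article, Objectives, the fourth hypothesis is that "Personalized acupuncture is more likely than letrozole, fixed acupuncture, and placebo letrozole to reduce the miscarriage rate and the risk of pregnancy complications". The Abstract and the Discussion repeat it against letrozole.

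The section Pregnancy loss rate defines loss as "pregnancy loss occurring from conception to 27 completed weeks of gestational age in this trial", and says this includes first-trimester loss and "pregnancy loss in the second or third trimester, biochemical pregnancy loss, and ectopic pregnancy". It then sets the denominator: "The pregnancy loss rate will be the proportion of women who abort among all participants who conceive".

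The neighbouring outcomes are built differently. Ovulation per participant, conception and pregnancy all use the women in the primary analysis as denominator. Conception is a positive serum β-HCG.

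The primary outcome, live birth, is "defined as delivery of any viable infant after 28 weeks of gestation". Follow-up of pregnancies says that biochemical and ectopic pregnancies are recorded, as are intrauterine losses before and after 20 weeks, stillbirths included.

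Data analysis compares a miscarriage rate between arms by relative risk with 95% confidence interval and chi-square test. It also names abortion as a binary outcome for logistic regression. Neither term is defined and neither has a stated denominator.

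**The concern.** There are two linked problems.

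The first is the comparison. Hypotheses 1 to 3 say that the arms will differ in ovulation and live birth, so the women who conceive in each arm are expected to be different groups. A difference in loss between those groups mixes any effect on loss with a difference in who became pregnant. Loss per conception is a sound descriptive rate. It is not a randomized test of whether a treatment reduces miscarriage.

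The second is the counting. The loss window, the listed components, the numerator and the live birth definition do not fit together. Two analysts could classify the same pregnancies differently, and some recorded outcomes belong to neither of the two defined categories.

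At stake is a published statement that personalized acupuncture lowers miscarriage, one of the four stated hypotheses, when the difference could come from who conceived or from how losses were sorted.

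**Working it through.** **Plan's own figure.** The article gives no expected rate, sample size or power for pregnancy loss. Its 250 per group concerns live birth and is reproduced by 25% versus 15% (two-sided 0.05, 80% power, pooled variance): [1.960 × √(2 × 0.20 × 0.80) + 0.842 × √(0.25 × 0.75 + 0.15 × 0.85)]² / 0.10² = 250. That figure is not affected here.

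**Inputs from Sample size calculations.** Live birth of 35% (letrozole), 25% (personalized), 15% (fixed) and 5% (placebo); 275 enrolled per arm.

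**Assumption.** Loss risk among conceivers, which the article does not give: 20% to 40%.

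**Step 1: size of the conditional groups.** Conceivers = 275 × live birth rate / (1 − loss risk).

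| Arm | Loss 20% | Loss 30% | Loss 40% |
|---|---|---|---|
| Letrozole | 120 | 138 | 160 |
| Personalized | 86 | 98 | 115 |
| Fixed | 52 | 59 | 69 |
| Placebo | 17 | 20 | 23 |

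With a common loss risk the groups differ up to sevenfold (35/5).

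**Step 2: selection with no treatment effect on loss.** Suppose every woman who would conceive on personalized acupuncture would also conceive on letrozole, with a 25% loss risk on either. Letrozole adds further conceivers with loss risk q. Live birth is held at the protocol's 25% and 35%.

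- Personalized conception: 0.25 / 0.75 = 33.3%. Loss per woman randomized: 0.333 × 0.25 = 8.3%.
- Additional letrozole conceptions: 0.10 / (1 − q).
- Letrozole loss per conception: (0.333 × 0.25 + additional × q) / (0.333 + additional).
- For q = 45%: additional = 0.10 / 0.55 = 0.182, and loss = (0.0833 + 0.0818) / 0.515 = 32.1%.

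| q | Letrozole conception | Letrozole loss per conception | RR per conception | Letrozole loss per woman randomized | RR per woman randomized |
|---|---|---|---|---|---|
| 15% | 45.1% | 22.4% | 1.12 | 10.1% | 0.83 |
| 25% | 46.7% | 25.0% | 1.00 | 11.7% | 0.71 |
| 35% | 48.7% | 28.2% | 0.89 | 13.7% | 0.61 |
| 45% | 51.5% | 32.1% | 0.78 | 16.5% | 0.50 |

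RR is personalized over letrozole. The per-conception ratio moves to either side of 1 with no effect on loss.

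**Step 3: does loss per woman randomized solve it?** No. The last column is below 1 in every row. With a common loss risk L, loss per woman randomized is live birth × L / (1 − L), so the ratio between arms is the ratio of live birth rates: 25/35 = 0.71 against letrozole and 25/5 = 5.0 against placebo. That contrast is randomized, but here it reflects conception alone.

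**Step 4: the definitions side by side.**

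- The window closes at 27 completed weeks, before 28 weeks and 0 days. The same sentence includes "pregnancy loss in the second or third trimester". If the third trimester starts at 28 weeks, no third-trimester loss can fall inside the window. The article does not define trimesters; with a start at 27 weeks the wording would be ambiguous rather than contradictory.
- Live birth is "delivery of any viable infant after 28 weeks of gestation". A fetal death from 28 weeks is outside the loss window and is not a live birth, yet Follow-up of pregnancies records stillbirths. This gap depends on no trimester convention.
- The numerator, women who abort, does not plainly cover the biochemical and ectopic losses that the definition lists.
- Hypothesis 4 and Data analysis speak of miscarriage, the outcome section of pregnancy loss, and the logistic model of abortion. Only pregnancy loss is defined.

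**The case against.** The strongest reply is that loss per conception is a legitimate, familiar rate for a secondary outcome, and that the randomized companions already exist: live birth is analysed by intention to treat, and conception and pregnancy use all women in the primary analysis. Analysis sets may be specified in a fuller document. Late fetal deaths are not overlooked either. They are recorded, pregnancy loss after 12 weeks is a serious adverse event, and fetal events are reported from 20 weeks through birth. Much of this stands. It limits the point to what hypothesis 4 can conclude and how outcomes are sorted. It does not make the defined rate a randomized comparison or close the gap at 28 weeks.

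Some stronger readings are tempting, and the documents do not support them.

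- A reader might infer that the conditional rate is the only pregnancy-loss analysis. It is the only loss rate defined. Data analysis also compares a miscarriage rate and models abortion, with body mass index and site among the explanatory variables, and gives no denominator for either. Linking miscarriage to the defined pregnancy loss is itself an inference.
- A reader might infer that the bias must favour personalized acupuncture. The loss risks above are assumed, and the direction reverses when the additional conceivers have the lower risk.
- A reader might infer that loss per woman randomized should become the test of hypothesis 4. In the example with q = 45% it gives 0.50, further from 1 than the 0.78 per conception, with no effect on loss.
- A reader might infer that the primary outcome is left undefined for stillbirths or early deliveries. For live birth, a stillbirth or a delivery before the limit is simply a non-event.

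**Conclusion.** The point holds in a limited form. Hypothesis 4 is causal, and the one loss rate defined for it is conditional on a post-randomization event that the trial itself expects to differ by arm. The comparison is non-randomized and can err either way: relative risk 0.78 to 1.12 with no effect on loss. That range rests on assumed loss risks (25%, and 15% to 45% in the additional conceivers), on the protocol's live birth rates, and on letrozole conceivers including all women who would conceive on personalized acupuncture. It illustrates the problem and does not predict the result.

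The inconsistency between the 27-week window and third-trimester loss rests on the usual 28-week start of that trimester. The unclassified fetal deaths from 28 weeks, the numerator that does not match its components, and the undefined terms in Data analysis follow from the text alone. No sample-size figure or primary result changes.

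**What to change.** 1. Make Follow-up of pregnancies, Primary outcome and Pregnancy loss rate agree on one gestational cut-off.
2. Assign every conception to exactly one class: live birth, pregnancy loss or stillbirth. Name biochemical and ectopic losses in the numerator, and say where a live-born infant delivered before the cut-off is counted.
3. Use that one term, with its denominator, in Objectives and Data analysis in place of miscarriage and abortion.
4. Report loss per woman randomized and per conception, beside conception and live birth per woman randomized.
5. Label the per-conception comparison as non-randomized. Do not use loss per woman randomized alone as the test of hypothesis 4, because it falls when fewer women conceive. Claim reduced miscarriage from neither rate alone.

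The cost is wording, a few more table rows and a more cautious conclusion on hypothesis 4. No new data are needed, since the pregnancy outcomes are already to be collected.
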